### Sample size

Following IMMPACT (Initiative on Methods, Measurement, and Pain Assessment in Clinical Trial) [25] recommendations for clinical trials involving chronic pain, we considered our primary outcome measure to be pain intensity changes, assessed through a VAS. We achieved a sample size of 15 subjects (G*Power 3.1), considering a reduction of 50 % (effect size of 0.5), a study power of 80 %, an alpha value of 5 % (*P* < 0.05), and six measures (three pre- and post-measures) on three intervention groups (placebo, and tDCS 1 mA and 2 mA).

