## Methods

### Study design

This is a randomized, controlled crossover double blind study with one group undergoing three different interventions. Treatment order will be determined randomly. The CONSORT guidelines from 2010 to clinical trials will be used to guide the procedures [20].

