### Statistical methods

The data will be recorded and analyzed by a blinded biostatistician. First, a descriptive analysis of variables will be performed. Data distribution will be analyzed using the Shapiro-Wilk test. To check carryover effects between sessions, we will carry out a *t*-test or a Wilcoxon rank sum, depending on the normal distribution.

Outcome measures will be compared both between and within groups considering pre- and post-interventions with repeated measures analysis of variance or nonparametric correspondence tests (Friedmann and Mann–Whitney tests). Clinical data will be correlated to EEG data through correlation tests (Spearman or Pearson). Significance will be established at an alpha value of 5 %, with a study power of 80 %. All data will be analyzed with intention-to-treat.

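### The sample-size statement treats a 50 % pain reduction as a standardised effect of 0.5, so 80 % power is not established for active versus sham with 15 subjects

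*Protocol article*

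**What the plan says.** The Sample size section takes VAS pain intensity as the primary outcome and reports 15 subjects from a named power program, "considering a reduction of 50 % (effect size of 0.5), a study power of 80" per cent, with a 5 % alpha. The remaining inputs are "six measures (three pre- and post-measures) on three intervention groups", listed as placebo, 1 mA and 2 mA. The section gives no SD, no within-patient correlation and no name for the effect-size metric.

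The Study design section describes a "crossover double blind study with one group undergoing three different interventions", and the Control group section says each subject serves as their own control. The Outcomes section uses 50 % as the threshold for satisfactory clinical improvement and defines the primary outcome through weekly averages of a daily pain diary. Statistical methods repeats the power figure: "Significance will be established at an alpha value of 5 %, with a study power of 80" per cent.

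**The concern.** The 50 % is a clinical threshold on a percentage scale, and the 0.5 is a standardised quantity. The text puts one in brackets after the other as if they were the same, and only the digits agree. Converting one to the other needs an SD, which is not given.

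The threshold also describes a fall from baseline under one condition. The trial has a sham period, so the comparison that tests the treatment is active minus sham. If sham also lowers pain, the difference between conditions is smaller than the fall under active stimulation.

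Finally, the calculation speaks of three groups, while the design has one group under three conditions. If three groups were entered literally, the power figure belongs to a different design.

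This is the only justification offered for 15 subjects, and the 80 % is stated twice. A null result could be reported as coming from a trial with established 80 % power when the document does not support that.

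**Working it through.** **Inputs from the protocol article.** N = 15, effect 0.5, power 80 %, alpha 5 %, six measures and three intervention groups (Sample size); entry VAS of 4 or more on a 10 cm scale (Eligibility criteria; Visual analog scale).

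**Assumptions, not in the document.** Correlation 0.5 and sphericity for the repeated-measures model; the SDs of the within-patient difference used in step 3.

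**1. Reproducing 15.** Read 0.5 as Cohen's f, with k = 3 groups, m = 2 measures each (pre and post, so 3 × 2 = 6), ρ = 0.5, and the group-by-time interaction test:

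- λ = f²·N·m/(1 − ρ) = 0.25 × N × 2/0.5 = N
- df1 = (k − 1)(m − 1) = 2; df2 = (N − k)(m − 1) = N − 3
- N = 13: power 0.79. N = 14: power 0.84. N = 15: power 0.87.

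The minimum is 14, which becomes 15 when rounded to three equal groups of five. The stated figure is reproduced, but by a parallel-group model.

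A one-group model with f = 0.5 and three measures at ρ = 0.5 needs 9 subjects; with six measures it needs 6. The three-measure version reaches exactly 15 at ρ = 0 (power 0.82), so a one-group route to 15 also exists.

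**2. The conversion.** A 50 % reduction from baseline B is 0.5·B cm. As a standardised difference it is d = 0.5·B/SD. Setting d = 0.5 gives SD = B. At B = 4 the reduction is 2 cm and the required SD is 4 cm; at B = 6 the required SD is 6 cm. Nothing in the document supports such an SD.

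**3. Power for the comparison of interest.** For one active-versus-sham contrast in 15 subjects, use the two-sided 5 % paired t test: dz = Δ/SD_diff, noncentrality dz·√15, 14 df. Take Δ = 2 cm, the halving of VAS 4, as an illustrative difference between conditions:

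| SD of within-patient difference (assumed) | dz | Power at n = 15 | n for 80 % |
|---|---|---|---|
| 2 cm | 1.00 | 95 % | 10 |
| 2.5 cm | 0.80 | 82 % | 15 |
| 3 cm | 0.67 | 67 % | 20 |
| 4 cm | 0.50 | 44 % | 34 |

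If 0.5 was meant as half an SD of the within-patient difference, the last row applies whatever the value in cm.

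**4. What 15 subjects can detect with 80 % power.** Solving for dz gives 0.78 at two-sided 5 % and 0.88 at two-sided 2.5 % (alpha split over two active-versus-sham contrasts). At 5 % this is 0.78 × 2 = 1.6 cm for an SD of 2 cm, or 0.78 × 3 = 2.3 cm for an SD of 3 cm.

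**The case against.** Four points can be made for the plan.

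*The stated 15 does reproduce.* This stands. The text itself glosses the measures as "six measures (three pre- and post-measures"), which reads naturally as three conditions, each pre and post. A reader who enters six measures in each of three groups gets 27, 9 or 9 (between, within, interaction) and might infer that the figure cannot be reproduced. That inference rests on a less natural reading of the inputs.

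*Intervention group may only mean condition.* This stands in part. The article uses the phrase loosely elsewhere, for example when it says the same electrodes are used in all intervention groups, and its design sections are clear that there is one group. A reader might infer that the calculation certainly assumed three samples of five. The document does not say so, and a one-group model at zero correlation also gives 15. The three-group route is the likelier one, because it matches the pre/post wording and needs only an ordinary correlation.

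*The trial may be adequately powered.* This stands. A reader might infer from the 44 % figure that the trial is underpowered. That figure needs an SD of 4 cm for a 2 cm difference, or a target of half an SD. With an SD of 2 or 2.5 cm, power exceeds 80 %. Taking f = 0.5 at face value in a one-group model with three measures and correlation 0.5 gives 99 %, so correcting the design alone would raise power.

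*An article may leave the SD and correlation to a fuller document.* Their absence alone would not be a finding. The printed conversion is different: it is wrong as a general statement, and further detail elsewhere would not make a percentage into a standardised effect. Under any metric, the conversion needs an SD.

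**Conclusion.** The point holds in a limited form. Equating a 50 % reduction with an effect size of 0.5 has no basis in the document, and it concerns a within-condition change instead of the active-minus-sham difference. That alone means the 80 % in Sample size and Statistical methods is not established for the comparison the trial is built to make. The possible use of a three-group model adds to this but is not needed for the conclusion.

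Actual power is unknown. It runs from 95 % to 44 % for a 2 cm difference over assumed SDs of 2 to 4 cm. What can be said without knowing the SD in cm is that 15 evaluable subjects give 80 % power for 0.78 SD of the within-patient difference at two-sided 5 %. This assumes a paired comparison with approximately normal differences.

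One further mismatch matters for the repair. The six measures correspond to the VAS readings taken before and after each session (Table 1), whereas Outcomes defines the primary outcome by weekly diary averages. Any SD used must belong to the diary average.

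**What to change.** Keep 15 subjects and rewrite the statement:

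- Delete the effect size of 0.5 as the translation of 50 %.
- Describe the design as one group under three conditions, not three groups.
- State the target as an active-minus-sham VAS difference in cm on the weekly diary average, with the SD of the within-patient difference and its source.
- Replace the 80 % claim in both Sample size and Statistical methods with the sensitivity of the actual design.

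Suggested wording: *With 15 evaluable subjects, a two-sided 5 % paired comparison of active with sham stimulation has 80 % power to detect a difference of 0.78 SD of the within-patient difference in weekly mean VAS (0.88 SD at 2.5 % for each of two comparisons). With an SD of y cm [source], this is x cm.*

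The values of x and y must come from the investigators; without a sourced SD, a range should be shown. The cost is wording only: no added subjects or visits. The stated sensitivity may become less favourable than the present 80 %, and it falls further if fewer than 15 subjects are evaluable.

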### Recruitment

The subjects will be identified from the database of a public dental reference center (COAT – Faculty of Dentistry, Federal University of Bahia, Brazil).

### Allocation of interventions

Subjects will be consecutively randomized in order of the interventions using the tool from randomization.com (DallalGE, http://www.randomization.com). This study will use the second generation suggested for crossover studies. Only the investigators assigned to apply tDCS will have access to the randomized list. This list will be opened only when all data are available and analyzed, unless a subject has a side effect that justifies the interruption of the procedure.

### Data collection procedure

After COAT institutional authorization, subjects will be contacted by phone to ascertain their interest. All interested participants will complete a pre-screening questionnaire. Each subject will be scheduled for an appointment in order to further determine if they meet the inclusion criteria. If they do, they will sign an informed consent and be formerly enrolled in the study.

Women of childbearing age will be required to take a urine pregnancy test during the screening process. If a subject becomes pregnant during the course of the study, she will be withdrawn. During this initial appointment, the subject will be asked to complete a daily pain VAS diary for 7 days. The average VAS score from this data will be used as a baseline pain value.

During a second visit (T2) all clinical and neurological assessments will be performed before and after the tDCS stimulation. The clinical assessments will be measured by VAS pain scores, anxiety measures, and quantitative sensory tests. Neurophysiological assessment will be measured by using an EEG to analyze cortical activity. Each patient will be clinically and neurologically assessed before and after the treatment session resulting in six data collection points (T2 to T7).

All subjects will be treated during a single session for three different interventions (IA, IB,or IC) with a washout period of 7 days between treatments in order to avoid any residual effects. As reported earlier, a single tDCS session usually is able to modify cortical excitability for 1 hour after stimulation [22, 23].

### Procedure details

Recently, a new version of RDC/TMD, now called Diagnostic Criteria for Temporomandibular Disorders (DC/TMD), was published [26]. However, since the new DC/TMD was not translated and validated into Brazilian Portuguese, we have decided to use the already-validated Brazilian version from 2004 [27]. This instrument will only be used to determine inclusion criteria.

RDC/TMD evaluation has two axes, one for assessing clinical characteristics (Axis I), and the other for assessing the psychosocial aspects (Axis II). As the specific instrument used to assess anxiety and depression will be the STAI scale, only Axis I of RDC/TMD will be used. The RDC/TMD has three diagnostic groups: (1) muscle disorders; (2) disc displacements; (3) arthralgia/arthritis/arthrosis [28]. Subjects who present only with muscle disorders will be included.

#### Visual analog scale (VAS) for pain

The VAS allows us to convert subjective sensations, such as pain, into numerical data. A 10-cm scale, where 0 cm is no pain and 10 cm is the worst imaginable pain, will be used, and the subjects will be asked to mark a point on the scale representing their pain intensity. This instrument will be completed everyday in the 7-day period after their acceptance. An average pain intensity score will be calculated as a baseline for the first treatment intervention. Averages for each week will be used to analyze if there will be any treatment carryover effect. The VAS scores will be recorded before and after each treatment session to verify treatment effect.

#### State-Trait Anxiety Inventory (STAI)

The STAI is used to evaluate objectively both aspects of anxiety: trait and state. Analyzing trait will show the personality, auto image, and the way that the subject realizes and perceives threatening situations. State anxiety is a transitory emotional state, in response to environmental stimuli such as tachycardia, sweating, nausea, and cramps. The questionnaire addresses 20 possible sensations for each. We will analyze values from 1 to 4, where 1 is never, 2 sometimes, 3 often, and 4 always. The results reveal whether the subject tends to present low levels of anxiety (20–40 points), middle levels of anxiety (41–60 points), or high levels of anxiety (61–80 points).

#### Quantitative sensory testing

Mechanical perception and pain threshold will be tested using Semmes-Weinstein monofilaments (0.008 to 300 g/mm^2^). Monofilament application will be at a masseter tender point with the control being the contralateral thenar area (the palm of the hand at the base of the thumb). Hairs will be applied gradually, until the subject perceives the stimulus (sensory perception threshold). The intensity will be increased until the subject describes it as painful (pain threshold). The thresholds will be taken at the lowest force that causes sensory/pain perception. The side of the most painful masseter will be used for both assessments.

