### Outcomes

The primary outcome of this study will be the extent to which this method will change baseline pain intensity (VAS). The subjects will record their experience on a daily basis in a pain diary. A weekly response average will be calculated before the first intervention and after each session. The averages will be used to compare the VAS values before and after each intervention. A decrease of 50 % will be considered a satisfactory clinical improvement.

Secondary outcomes will be the degree of change from baseline in power density of alpha and theta EEG bands. Other outcome measures will be pain pressure threshold (PPT), mechanical pain thresholds (MPTs), and STAI. Increase in PPT and mechanical thresholds indicate an improvement in subject pain condition; a decrease in STAI indicates a better emotional state.

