#### Pain pressure threshold (PPT)

PPT will be determined by applying blunt pressure by a hard-rubber probe, using an approved device (EMG 1630WF, EMG System, Brazil). During the test, pressure will be applied to the same area as in the mechanical perception and pain threshold tests, with increasing intensity at a rate of 1 kg/second. When the subject reports that he/she feels any pain, the procedure will be stopped. A computer program (EMGLab, EMG System, Brazil) will automatically record the value. This procedure will be repeated three times to achieve an average.

These tests will take approximately 7–10 minutes to be completed.

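### The monofilament thresholds are scored from an ascending series with no repeat or average, although pressure pain threshold is averaged over three readings, and the test point is not tied to one visit

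*Protocol article*

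**What the plan says.** All references are to the protocol article.

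- **Monofilament scoring** (Quantitative sensory testing). Filaments are applied in rising order, first until felt and then until painful. The scoring rule is "The thresholds will be taken at the lowest force that causes sensory/pain perception". The number of series is not given and no average is mentioned.
- **Site and side** (same section). "Monofilament application will be at a masseter tender point with the control being the contralateral thenar area". The side is set by a separate sentence: "The side of the most painful masseter will be used for both assessments". Neither sentence names a visit.
- **PPT** (Pain pressure threshold). For this test "pressure will be applied to the same area as in the mechanical perception and pain threshold tests", and "This procedure will be repeated three times to achieve an average".
- **Rank** (Outcomes). "Other outcome measures will be pain pressure threshold (PPT), mechanical pain thresholds (MPTs), and STAI". Pain on the VAS is primary, and EEG band power is secondary. A rise in the mechanical thresholds is read as improvement.
- **Schedule** (Table 1; Data collection procedure). Sensory testing is done before and after stimulation at V2, V3 and V4, which gives six test occasions, T2 to T7.

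**The concern.** Two neighbouring sections describe two pain thresholds, at the same area and in similar detail, but handle reading error differently. PPT has a stated averaging rule. The monofilament rule picks out one force, the lowest that is felt or felt as painful. Taken at face value, that is a single reading per test occasion. If several series are run after all, the wording points to the minimum over them. A minimum drifts downwards as series are added, so it does not estimate the same quantity as a mean.

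The comparison of active with sham stimulation is a difference of two pre-post changes, so it contains four readings per subject and reading error enters four times. With 15 subjects, extra error lowers the chance of seeing a real shift in MPT.

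The second part concerns the site. The text fixes a type of point and a rule for the side, but not that both are chosen once per subject. If the tester looks for the most painful side or a tender point afresh after stimulation, the post reading may come from different tissue than the pre reading. PPT uses the same area and has the same gap.

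**Working it through.** **1. Inputs.** From the article: n = 15 (Sample size), filament range 0.008 to 300 g/mm² (Quantitative sensory testing), three PPT readings averaged. The article gives no SD, reliability or expected shift for MPT, and no power figure for it, so there is no stated figure to reproduce. Everything else below is assumed.

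**2. Effect of averaging.** With independent errors, the error variance of a mean of *k* readings is σ²/*k*. For *k* = 3 the error SD is multiplied by 1/√3 = 0.577. Total variance is multiplied by R + (1 − R)/3, where R is the single-reading reliability:

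| R (assumed) | Variance factor | Reliability of mean of 3 |
|---|---|---|
| 0.5 | 0.667 | 0.75 |
| 0.7 | 0.80 | 0.875 |
| 0.9 | 0.933 | 0.964 |

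**3. Power for active minus sham.** Let σs be the SD between test occasions and σp the SD between passes on one occasion, both in log10 units. Assume 20 filaments evenly spaced on the log scale. The range is log10(300/0.008) = 4.574, so the step is 4.574/19 = 0.241 and its rounding variance is 0.241²/12 = 0.0048. Four readings enter, so

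Var(D) = 4 × [σs² + (σp² + 0.0048)/*k*].

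Power comes from the noncentral *t* distribution with 14 degrees of freedom, two-sided 5 %, standardised effect = shift/√Var(D).

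Example with σp = σs = 0.2 and shift 0.35:
- *k* = 1: 4 × (0.04 + 0.0448) = 0.339, SD 0.583, effect 0.60, power 0.58.
- *k* = 3: 4 × (0.04 + 0.0149) = 0.220, SD 0.469, effect 0.75, power 0.77.

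| Shift | σp | σs | Power, 1 series | Power, 3 series | Gain (points) |
|---|---|---|---|---|---|
| 0.35 | 0.3 | 0.15 | 0.45 | 0.77 | 32 |
| 0.35 | 0.2 | 0.2 | 0.58 | 0.77 | 19 |
| 0.35 | 0.1 | 0.2 | 0.77 | 0.84 | 8 |
| 0.35 | 0.1 | 0.4 | 0.33 | 0.34 | 1 to 2 |
| 0.20 | 0.2 | 0.4 | 0.13 | 0.14 | 1 |
| 0.10 | 0.2 | 0.2 | 0.10 | 0.12 | 2 to 3 |
| 0.60 | 0.1 | 0.2 | about 1 | about 1 | near 0 |

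Simulating the model with 20,000 trials per setting, and rounding each reading up to the next filament, agrees with these values to about one percentage point.

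**4. Another route.** Take a single-series standardised effect of 0.5, which gives power 0.44 at n = 15. If 25 %, 50 % or 75 % of the variance of the difference is pass-to-pass error, three series raise power to 0.51, 0.60 or 0.72.

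**5. Site.** Write a reading as true threshold + site effect + error.
- Same point before and after, whichever visit: the site effect cancels in that visit's change.
- Point *a* before and point *b* after: the change contains (site *b* − site *a*), which does not cancel.
- Choosing the worst point afresh before every test lowers pre and post readings alike on average, so it mostly drops out of the mean contrast, but the variation between the chosen points stays.

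Only a change of point within a session therefore does appreciable harm.

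**The case against.** The article does not say that one series is run; this is the natural reading of a rule without repeats, and not an explicit statement. A journal article may leave the number of series, and how a test point is found again, to an operating manual. That stands as a caution. It does not remove the point, because the article gives a complete scoring rule for one threshold and a different one, with averaging, for its neighbour.

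Three stronger readings are tempting, and the text does not support them.

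- *The site is defined only by the more painful masseter.* It is not. That sentence fixes the side. The site is a masseter tender point with a thenar control. Since PPT shares the area, site cannot make MPT noisier than PPT.
- *Changes of side across the three visits spoil the comparison of interventions.* They largely cancel in each visit's own change. The text can also be read as one side per subject throughout.
- *The plan demonstrably loses a large amount of power, on a coarse filament grid.* The article gives a range but no count or spacing of filaments, and no variability. The gain nearly vanishes when variation between occasions is large, or when the shift is very small or very large.

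Time is a fair counterargument. Post-stimulation VAS, STAI, EEG and sensory testing share a window in which the article expects the effect to last about 1 hour (Data collection procedure) or up to 1.5 hours (Control group).

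**Conclusion.** The point holds as a minor, cheap improvement. As written, the monofilament rule uses less information than the PPT rule beside it, and a mean of three series is more precise than a single pass and, unlike a minimum over repeats, does not drift with the number of series. The direction of the gain needs only that pass-to-pass errors are not perfectly correlated. Its size cannot be taken from the article: at n = 15 it runs from about 1 to about 30 percentage points over the assumed settings, and close to zero where power is already near 1.

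The site gap affects both MPT and PPT, but matters mainly if the point is chosen again within a session. Whether that would happen is not stated. Nothing here touches the VAS primary outcome or the sample size.

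**What to change.** - In Quantitative sensory testing, state that three ascending series are run and that the score is their geometric mean (mean of log force), in place of the lowest force.
- In that section and in Pain pressure threshold, state that the side and one masseter point are chosen once at V1, recorded, and reused at T2 to T7 whichever side hurts more on the day.

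Fixing the point costs essentially nothing. The extra series add some repeated stimulation and a few minutes to each testing block, beyond the 7–10 minutes now given. A ceiling is 2 × 7 = 14 to 2 × 10 = 20 minutes, if all of that time were monofilament work; the true figure is lower if that time also covers PPT, which already has its three readings. The order of post-stimulation tests should be checked so that the added time stays within the expected duration of effect. Recruitment is under way, so the clarification should take effect for subjects not yet tested, to keep one scoring rule within each subject, and the date of the change should be recorded.
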